#### Analysis

Analysis of primary outcome measures will determine whether the provision of S&D reduction training for clinic staff and the YWHC intervention for AGYW will increase PrEP readiness, PrEP uptake, and PrEP adherence, and SRH uptake.

#### Clinic level

AGYW service utilization will be assessed and analyzed through clinic level data at each of the 12 study clinics during an 8-month period pre- and post-training (e.g., HIV testing; number of PrEP prescriptions). Baseline and follow-up clinic staff surveys will be analyzed to examine changes in attitudes and stigma at the clinic level. Initial analyses will be descriptive and evaluate group differences comparing intervention and control clinics using unpaired t-tests with unequal variance or nonparametric tests, as appropriate. Using multilevel modeling approach, we will investigate and account for clustering at the clinic level. We will use difference-in-differences (DD) methods as done in another South African study to examine utilization of services by AGYW and staff attitudes and behaviors in the 8 months between intervention and control clinics [60]. The DD estimator reflects the average change in clinics that received S&D reduction training, after the average change in utilization in control clinics is subtracted, assuming parallel trends in clinics over time had the S&D reduction training not been implemented. DD estimates will be calculated for each outcome separately; models will include covariates for time (pre- vs. post-intervention), treatment (training vs. no training) and an interaction between the two. The clinics identified are similar in size, services, and populations served. Any clinic features for which we cannot achieve balance through the design will be included as covariates in the multivariable DD analyses. A stigma score will constitute one primary outcome for these analyses. To examine short-term changes between pre-intervention and 4-month follow-up, DD methods can be used to compare the average change in stigma scores in clinics that received S&D reduction training, removing any changes observed in control clinics. We will use generalized estimating equations (GEE) [61] to examine provider-level stigma scores measured at 4- and 8-month follow-up comparing trained and untrained clinics, accounting for clustering at the clinic-level.

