### Randomization

Stratified randomization was conducted via SAS Software after clinic selection was finalized. The sample of 12 clinics was first grouped into three strata (peri-urban/city, peri-urban/provincial, and semi-rural/provincial) based on geographic location type (peri-urban vs. semi-rural) and clinic administration type/jurisdiction (city vs. provincial), with four clinics in each stratum. Within each stratum, clinics were then randomly assigned to study conditions based on a 1:1:1:1 allocation. Because there may be important differences pertinent to the outcomes that cannot be made homogenous, such as geographical region, stratified randomization was conducted to achieve even distribution of these factors across study arms. This reduces variability in the estimation of the intervention effect, with resulting increases in power/precision of estimates [49].

The six clinics randomized to receive the S&D reduction training will participate in workshops aimed to reduce clinic staff’s S&D attitudes and behaviors toward AGYW. For the 6 clinics randomized to the YWHC, AGYW participants recruited from communities in clinic catchment areas will be asked to participate in two workshops.

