### Study procedures

#### Data collection: clinic level

At baseline, all clinics (those receiving training and those receiving no training) complete a clinician (e.g., physicians, nurses) or clinic support staff (e.g., receptionists, clerks) survey assessing (after providing informed consent) SRH knowledge and service provision, attitudes toward PrEP and AGYW seeking PrEP, and observations of stigmatizing and discriminatory behavior in their clinic toward AGYW seeking services for SRH, HIV, and PrEP (see Clinician Questionnaire & Support Staff Questionnaire in Supplementary Files 1 & 2). This survey is re-administered at 4- and 8-months post baseline. Given the staff turnover and availability and to ensure to anonymity, staff surveys are not linked across time points; consequently, changes at the clinic level are assessed. Clinic support staff surveys have been translated into a local language, Setswana, for easier comprehension. A clinical audit is also being conducted at baseline and 4-month and 8-month follow-up by research study staff to collect information on service utilization, including the number of AGYW receiving health services (including HIV, birth control, and antenatal care) from clinical records; PrEP prescriptions from pharmacy and study nurse records; availability of birth control methods; presence of clinic guidelines and standards of practice for serving sexually active AGYW; working hours that are convenient for AGYW, as well as adequate staff to provide youth friendly services. This audit is conducted across all study clinics.

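### Entering an unbalanced baseline clinic feature as a covariate does not protect the difference-in-differences estimate; only its interaction with time can

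*Protocol article*

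**What the plan says.** Under Analysis, Clinic level, the protocol article specifies the DD models term by term: "models will include covariates for time (pre- vs. post-intervention), treatment (training vs. no training) and an interaction between the two". The estimator is interpreted "assuming parallel trends in clinics over time had the S&D reduction training not been implemented". For imbalance it adds: "Any clinic features for which we cannot achieve balance through the design will be included as covariates in the multivariable DD analyses". No feature-by-time term is named.

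Two kinds of data feed these models. Utilization is a panel of the same clinics: "AGYW service utilization will be assessed and analyzed through clinic level data at each of the 12 study clinics". The surveys are anonymous repeated cross-sections: "staff surveys are not linked across time points; consequently, changes at the clinic level are assessed". Clustering is to be handled in the model: "Using multilevel modeling approach, we will investigate and account for clustering at the clinic level".

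The Randomization section explains the stratification by noting that "there may be important differences pertinent to the outcomes that cannot be made homogenous". Each of the three strata, formed from location and jurisdiction, holds four clinics allocated 1:1:1:1 to the four conditions.

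**The concern.** A DD estimate compares changes, so a feature that only shifts a clinic's level has already dropped out. A feature can distort the comparison only if clinics that have it change differently over time and it is unevenly split between trained and untrained clinics. A main effect describes level, so it cannot address that.

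The sentence is the section's only provision for imbalance that remains after stratification. If it is followed as written, a multivariable DD could be reported as adjusted while its estimate equals the unadjusted one. A stigma score is one primary outcome of these analyses, and only six clinics per training arm stand behind it.

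**Working it through.** The article gives no figure for this point, so there is none to reproduce.

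**Inputs.** From the article: 12 clinics, 6 trained and 6 untrained, seen before and after training; model terms as listed. Assumed: a binary baseline feature x held by 6 of the 12 clinics and unrelated to the strata; an effect γ of x on change of 0 to 0.6 SD; SD σ of other between-clinic variation in change of 0.2 or 0.3.

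**1. Algebra.** Let P be post, T training, u a clinic effect and δ the DD effect:

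Y = a + bP + cT + δPT + λx + u + e.

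Subtracting pre from post within a clinic gives change = b + δT + error. Both λx and u cancel, so the estimate of δ is the mean change in trained clinics minus that in untrained clinics, with or without x. Adding θ·x·P gives change = b + δT + θx + error, and only then can the estimate of δ move.

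**2. Check on simulated data.** Time-by-training estimate:

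| Layout | Without x | x as main effect |
|---|---|---|
| Linear clinic panel (OLS and random intercept) | 1.826 | 1.826 |
| Poisson log link, same layout | 0.4825 | 0.4825 |
| Surveys reduced to clinic means | – | shift about 1e-14 |

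In a separate 12-clinic panel the estimate was 0.0751 without x, 0.0751 with the main effect, and −0.109 with feature-by-time.

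**3. Conditional bias.** Suppose x is held by 4 of 6 trained and 2 of 6 untrained clinics, γ = 0.6 SD, and training has no effect. The bias is (4/6 − 2/6) × 0.6 = 0.20 SD, the same with x as a main effect. Feature-by-time removes it in expectation.

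**4. Layouts where the estimate can move.** Same imbalance and γ, no training effect:

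| Layout | Without x | Main effect | Feature-by-time |
|---|---|---|---|
| Unlinked staff, exchangeable GEE, 10–30 per wave, mean bias over 300 runs | 0.191 | 0.191 | −0.015 |
| Logit link, spurious log-odds DD | 0.185 | 0.198 | 0.000 |

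**5. Precision over allocations.** Let k be the number of trained clinics with x. The arm difference in prevalence is (k − 3)/3, which is also its correlation r with training.

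- Chance of an unequal split: 1 − 400/924 = 57%.
- Var(k) = 6 × ½ × ½ × 6/11 = 0.818, so Var(r) = 0.818/9 = 0.0909.
- Unadjusted variance: 0.0909γ² + σ²(1/6 + 1/6).
- Variance with feature-by-time: (σ²/3) × mean of 1/(1 − r²). That mean is (400 × 1 + 450 × 1.125 + 72 × 1.8)/922 = 1.123, omitting the 2 of 924 allocations in which x coincides with training arm.

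For γ = 0.6 and σ = 0.3: √(0.0327 + 0.0300) = 0.250 against √(0.0300 × 1.123) = 0.184, a ratio of 1.36.

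| γ | SD ratio, σ = 0.3 | SD ratio, σ = 0.2 |
|---|---|---|
| 0 | 0.94 | 0.94 |
| 0.1 | 0.96 | 0.98 |
| 0.2 | 1.00 | 1.06 |
| 0.3 | 1.06 | 1.20 |
| 0.6 | 1.36 | 1.75 |

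Simulation of the stratified scheme gave 0.250 v 0.184 and 0.216 v 0.123 at γ = 0.6, ratios of 1.36 and 1.76. Break-even is at γ = σ√(0.123/(3 × 0.0909)) = 0.67σ.

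**The case against.** **The wording.** The article says covariates, not fixed main effects, and its list of DD terms uses the same word for a group that includes an interaction. An article may leave the functional form to a fuller plan. This has some force, but the list names its one interaction explicitly and the imbalance sentence names none. A feature that the design could have balanced is one known at allocation. A baseline main effect is therefore the natural reading.

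**Time-varying features.** Some clinic features are re-measured: "A clinical audit is also being conducted at baseline and 4-month and 8-month follow-up by research study staff", and these include hours and staffing. Time-varying values do move a DD estimate (3.65 to 0.59 in one simulated data set). But values taken after training may be affected by it, so adjusting for them could remove part of the effect, and they are not what balance by design describes.

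**Does the rule do nothing at all?** A reader might infer this, and it goes too far. With 8–30 individual staff responses per clinic and wave (assumed), the main effect shifted the estimate by 0.03 on average (maximum 0.14) with a random intercept, though some of those fits gave convergence warnings, and by 0.04 (maximum 0.20) with GEE. One logit fit moved from 1.325 to 1.726. In OLS without clinic effects it cut the standard error from 1.354 to 0.580; with a random clinic intercept the standard error stayed at 0.554. So the estimate or its standard error can change. Step 4 shows that the feature-related bias is still not removed.

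**Which features.** Jurisdiction and location do not qualify: every stratum has two trained and two untrained clinics. The article also describes the clinics as comparable in size, which makes size a weaker candidate.

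**Size of the gain.** At γ = 0.6 one binary feature would explain about 50% (σ = 0.3) to 69% (σ = 0.2) of the between-clinic variance in change. At 0.1 the interaction makes the estimate slightly noisier. This stands, and it is why a range is given.

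**Conclusion.** The point holds for baseline features entered as main effects. In the clinic-level pre/post analyses the rule leaves the DD estimate exactly as it was; in staff-level and logit models it does not remove differential change related to the feature. A reader might infer that the planned DD is biased. The documents do not support that: training was randomized, so the unadjusted estimate is unbiased over allocations, and 0.20 SD applies only to a 4 v 2 split with a 0.6 SD effect on change.

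The general loss is precision. The SD of the unadjusted estimate is 0.94 to 1.76 times that with feature-by-time over the assumed range. The possible gain is large and the possible loss is about 6%, which justifies changing the sentence. The exact invariance needs no effect-size assumption; the size of the gain rests on the assumed γ, σ and prevalence of the feature.

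**What to change.** Replace the sentence on unbalanced clinic features with:

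> One or two baseline clinic features, named before the outcome data are seen and expected to predict change in the outcome, will be entered together with their interaction with time (feature × post) in the DD models; features measured after training will not be used for adjustment.

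Report the unadjusted DD alongside.

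The cost is one residual degree of freedom per feature. In the simple model of clinic changes, that takes 12 − 2 = 10 down to 12 − 3 = 9 for one feature. If the feature does not predict change, the SD of the estimate rises by about 6% (√1.123 = 1.06). With 12 clinics, more than one or two such terms cannot be afforded.

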#### Stigma and discrimination reduction training

After baseline data collection, marketing and planning, including the introduction of the training, are proposed for clinics randomized to receive the S&D reduction training so that time is allocated and protected for staff to attend the workshops. Although all clinic staff members are eligible and encouraged to attend, this study relies on clinic managers to approve who, among those interested, can take part in the assessments and training, as some clinic operations need to be maintained during this time. The HPP S&D reduction curriculum encourages all staff at all levels to be involved in the training workshops [41] because they are likely to interact with AGYW. For example, in South Africa, support staff such as receptionists and clerks often interact with AGYW because they serve as gatekeepers to clinicians.

The S&D reduction training incorporates important baseline findings for relevance and ownership through participatory activities addressing key drivers of clinic stigma toward AGYW seeking PrEP and birth control. This includes building awareness of AGYW stigma—its causes, forms and manifestations—reflecting on one’s own stigmatizing experiences and attitudes towards AGYW and developing a plan/pledge with actionable steps to reduce S&D in the clinic. The HPP curriculum [41, 42] has been adapted with respect to time, target audience, and type of stigma relevant to this study. Modifications include examples of AGYW seeking services in pictorial displays and other pictures to elicit conversation in the workshops to address various types of bias (see Table 1 for an overview of the S&D reduction training).

**Table 1 Tab1:** Overview of the S&D Reduction Training

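### The primary stigma score draws on two unlinked staff questionnaires, and no staff-type term is named, so a respondent-mix change that differs by arm would be confounded with the training effect

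*Protocol article*

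**What the plan says.** Under Data collection: clinic level, staff in all clinics "complete a clinician (e.g., physicians, nurses) or clinic support staff (e.g., receptionists, clerks) survey" at baseline, 4 months and 8 months. There is one instrument for each group ("see Clinician Questionnaire & Support Staff Questionnaire in Supplementary Files 1 & 2"), and the support-staff form is also available in Setswana. Because of turnover, availability and anonymity, "staff surveys are not linked across time points; consequently, changes at the clinic level are assessed".

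Under Stigma and discrimination reduction training, "this study relies on clinic managers to approve who, among those interested, can take part in the assessments and training".

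Under Analysis, Clinic level, "A stigma score will constitute one primary outcome for these analyses". For the DD analyses, "models will include covariates for time (pre- vs. post-intervention), treatment (training vs. no training) and an interaction between the two". In addition, "Any clinic features for which we cannot achieve balance through the design will be included as covariates in the multivariable DD analyses". For the short-term change, DD is to "compare the average change in stigma scores in clinics that received S&D reduction training, removing any changes observed in control clinics". A GEE then compares provider-level scores at 4 and 8 months between trained and untrained clinics, with clinic clustering as the only adjustment named.

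The article does not say how the score is constructed across the two forms. It gives no number of staff respondents, no SD for the score and no power figure for this outcome.

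**The concern.** Each wave is a new cross-section of whoever is available and approved to take part, so no change can be measured within a person. Receptionists and nurses may differ in their average score, because their attitudes differ or because they answer different forms. If so, a clinic's mean depends partly on the proportion of each group among that wave's respondents. Staff type is a characteristic of the respondent, and the model terms listed do not include it.

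There are three consequences:

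- In the DD analysis, a change in mix that occurs in trained clinics but not in control clinics, or to a different extent, would be counted as a training effect, in either direction.
- In the follow-up GEE, any difference in mix between the arms at 4 or 8 months would enter the comparison directly, because no baseline term is named.
- Even with no systematic shift, random variation in mix widens the interval around a comparison of only 6 with 6 clinics.

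A differential shift is conceivable. Managers decide who joins both the assessments and the training, and only trained clinics release staff for workshops and hold booster sessions to deal with turnover.

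**Working it through.** The plan gives no figure to reproduce for this outcome. Only the design is taken from the article: 12 clinics, 6 per training condition, unlinked waves, and the DD terms quoted above. All other inputs are assumptions.

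**1. Bias in DD.** Let g be the clinician-minus-support-staff difference in mean score (in SD units). Let s_T and s_C be the changes in clinician share from baseline to follow-up in trained and control clinics. If nobody's attitude changes:

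false DD effect = g × (s_T − s_C)

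- Same 20-point shift in both arms, g = 0.5: 0.5 × (0.20 − 0.20) = 0.
- 20-point shift in trained clinics only, g = 0.5: 0.5 × 0.20 = 0.10 SD.
- Low end, g = 0.2 and a 10-point shift: 0.2 × 0.10 = 0.02 SD.
- High end, g = 0.8 and a 30-point shift: 0.8 × 0.30 = 0.24 SD.

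A null simulation (12 clinics, 20 staff per clinic per wave, g = 0.5, 400 runs) agrees:

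| Shift in clinician share | Mean DD without staff type | Mean DD with staff type |
|---|---|---|
| 20 points, both arms | −0.004 | −0.004 |
| 20 points, trained only | 0.098 | −0.001 |

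The Monte Carlo standard error of the unadjusted means is about 0.01.

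**2. Bias in the follow-up GEE.** With no baseline term, the false effect is g times the arm difference in clinician share at that visit, whether that difference is new or was already there at baseline. For g = 0.5 and a 20-point difference it is again 0.5 × 0.20 = 0.10 SD.

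**3. Noise with no systematic shift.** Assume a within-group SD of 1, a clinic-level SD of true change of 0.15, n respondents per clinic per wave, and a clinic-by-wave SD of mix of 10 points. The variance of one clinic's change is then:

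- with staff type adjusted: 0.15² + 2/n
- unadjusted: the same plus 2 × g² × 0.10²

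Results:

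- n = 15, g = 0.5: 0.0225 + 0.1333 = 0.1558. The addition is 2 × 0.25 × 0.01 = 0.005, so the ratio is 1.03.
- n = 30, g = 0.8: 0.0225 + 0.0667 = 0.0892. The addition is 2 × 0.64 × 0.01 = 0.0128, so the ratio is 1.14.

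If the 10 points describe the underlying mix and respondents are sampled from it, binomial variance must be added. With an average share of one half this is (0.25 − 0.01)/n = 0.24/n:

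- n = 15, g = 0.5: the addition is 2 × 0.25 × (0.01 + 0.016) = 0.013, ratio 1.08.
- n = 30, g = 0.8: the addition is 2 × 0.64 × (0.01 + 0.008) = 0.023, ratio 1.26.

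Adjustment therefore reduces the variance by between 1 − 1/1.03 = 3% and 1 − 1/1.26 = about 20%. This ignores the small cost of estimating the staff-type slope.

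**4. Effect on the nominal 5% error.** In simulations of 3,000 trials per setting, the mildest case (n = 15, g = 0.5, 15-point shift in trained clinics only) gave a bias of about 0.07 SD and a rejection rate of 5.0%. The most severe (n = 30, g = 0.8, 25-point shift) gave a bias of about 0.19 SD and rejection of 13.6% in one run and 15.2% in another. With staff type in the model, bias was about 0 and rejection stayed between 4.2% and 5.7%.

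**The case against.** The strongest reply is that a journal article need not set out how a scale is scored or list every respondent-level covariate. The two questionnaires are in supplementary files that are not at hand, and a fuller plan may deal with both points. This stands for the construction of the score: a reader might infer that the article pools the two forms into one number, but it does not say so. One score drawn from staff surveys without a split suggests it. The term provider-level in the GEE sentence could, however, mean clinicians only, or there could be a score for each form.

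A reader might also infer that any change in who answers would be read as a change in stigma. For the DD analysis that is wrong: subtracting the control-clinic change removes whatever is common to both arms. All clinics are surveyed on the same schedule and staff at every level are encouraged to attend the training, so nothing in the article shows that the mix will move differently by arm.

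Nor is the covariate list expressly closed. It states what the models will include, and staffing mix could be argued to be a clinic feature. That argument is weak. The clause concerns features the design could not balance, whereas the mix of respondents changes from wave to wave.

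Finally, every magnitude rests on assumed inputs, and at the mild end there is no detectable error inflation. This is correct.

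The reply leaves one thing standing. The article goes beyond silence: it names the model and its terms for a primary outcome measured on changing respondents. For the AGYW models, by contrast, it provides for participant-level covariates where the arms differ.

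**Conclusion.** The point holds in a limited form. The article commits to staff-level models of a primary stigma score, apparently spanning two questionnaires and unlinked respondents, without naming staff type. DD protects against a mix change shared by both arms, but not against one that differs by arm. The follow-up GEE is open to any arm difference in mix at the visit.

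The size depends wholly on assumptions. The false effect is 0.02 to 0.24 SD for a gap of 0.2 to 0.8 SD and a 10- to 30-point shift in trained clinics only, and 0 if the shift is equal. The article does not support a claim that the primary result will be biased, or that the forms are certainly pooled. The case for change is that the adjustment removes this source of confounding if it arises, and gains some precision even if it does not. It is worth making, at medium confidence.

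**What to change.** Include staff type, as identified by the questionnaire completed, as a fixed covariate in every staff-level DD and GEE model of the stigma score. Report the training effect by staff type as supportive. State how the score is formed across the two questionnaires. If they score differently, standardise each form to its own baseline mean and SD before combining.

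Rebuilding the score from items common to both forms is not recommended here, because their overlap cannot be judged from the article.

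The cost is one extra model term and a little more analysis work. No new data are needed and anonymity is unaffected, since the form used is known for every response. Training is unlikely to change a person's staff type, so adjusting for it should not remove any of the real effect. The adjustment does not deal with selection within a staff type, such as more willing nurses answering in trained clinics.
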